#### **Research background**

In 1992, Astrazeneca developed a new amide topical anesthetic, ropivacaine. It mainly works by blocking sodium ion entering the nerve fiber membrane and causing reversible block of impulses along the nerve fiber. In 1996, ropivacaine was first marketed in the Netherlands, and in 1998, ropivacaine entered the Chinese market. At present, the preparation for clinical use is ropivacaine salt (mesylate or hydrochloric acid) aqueous solution.

Local anesthetics may have a similar effect on excitable cell membranes such as brain cells and cardiomyocytes, and if excessive amounts of the drug rapidly enter the systemic circulation, the central nervous system and cardiovascular system will show signs and symptoms of toxicity. Intravenous ropivacaine was well tolerated in healthy volunteers, and clinical application suggested that ropivacaine had a good safety range. Indirect cardiovascular effects (hypotension, bradycardia) may occur with epidural use of ropivacaine, depending on the degree of parasympathetic block. Within the safe dose range, the effective duration of nerve block analgesia with infiltration of ropivacaine at the surgical site after surgery was only 8h, while the peak of postoperative pain in clinical patients was the first 3 days after surgery. The efficacy of ordinary ropivacaine aqueous solution was far from meeting the analgesic requirements of patients. Long-acting ropivacaine injection was ropivacaine free alkali oil solution, has the characteristics of drug loadings and slow release. In animal experiments, compared with the aqueous solution of ropivacaine salt, the dosage of long-acting ropivacaine injection was increased 3.4 times, the efficacy increased about 3-6 times. The result suggested that the peak time would cover clinical postoperative pain.

#### **Summary of preclinical studies:**

##### **Efficacy:**

① **Effect of long-acting ropivacaine injection on postoperative pain in rats:** when the dosage was 12mg/mouse, the analgesia of ropivacaine hydrochloride injection lasted for 4h, and 50% of animals died, 50% of animals responded to general anesthesia, which recovered within 2h; The analgesic duration of long-acting ropivacaine injection was 10h. ② **The blocking effect of long-acting ropivacaine injection on nerve conduction in anesthetized rabbits:** In ropivacaine mesylate injection group, local nerve conduction was almost completely inhibited about 5min after administration, and the effect lasted for 2~3h; Long-acting ropivacaine injection group 1(0.89mg/rat), normal saline group and blank solvent group had no effect. Long-acting

ropivacaine injection group 2(3mg/ rat) had a slower effect, and the inhibition duration of nerve impulse conduction was 12-16h. Compared with ropivacaine mesylate group, the sensory nerve block time was 6-7 times longer when the dose of long-acting ropivacaine injection was increased by 3.4 times, and the long-acting ropivacaine injection had a good sustained release effect. ③**The effects of long-acting ropivaine injection on the duration and latency of epidural anesthesia were as follows:** The duration of lower limb paralysis of ropivaine mesylate injection in control group was 4.6, 14.6 and 29.5min when rats were given equal doses (60, 180 and 600  $\mu$  g/ rat); The duration of lower limb paralysis in long-acting ropivacaine injection group was 15.4, 53.3 and 237.2min, respectively. Compared with the control group, the duration of epidural anesthesia in the long-acting ropivacaine injection group was 3.3, 3.6 and 8.1 times, and the long-acting ropivacaine injection significantly prolonged the effect of epidural anesthesia.

#### **Safety:**

The drug of long-acting ropivacaine injection adopts the free base form of ropivacaine, and the solvent system includes benzyl alcohol, benzyl benzoate, and soybean oil. Both the drug and excipients have a history of clinical injection, so their genetic and reproductive toxicity evaluation is safe. The clinical design dose of long-acting ropivacaine injection, whether as the main drug or as an excipient, exceeds the current clinical dose. Therefore, the key points of safety evaluation of long-acting ropivacaine injection are as follows: The acute toxicity of long-acting ropivacaine injection was evaluated by rats and dogs, and the indexes of blood, biochemistry and pathological changes of main organs were investigated. TK test was carried out at the same time. The experimental results showed that the safety of ropivacaine injection was very good under the current designed dosage conditions.

The evaluation results of irritation and wound healing showed that long-acting ropivacaine injection had recoverable local irritation and had no effect on wound healing, and the evaluation results of allergic reaction were good. Compared with ropivacaine hydrochloride injection, PK test results showed that long-acting ropivacaine injection could significantly reduce  $T_{max}$  and prolong  $MRT_{last}$  in vivo after equal doses injection, and reduced the cardiovascular and neurotoxicity caused by rapid release of ropivacaine solution. In conclusion, compared with ropivacaine hydrochloride injection, long-acting ropivacaine injection has a good safety guarantee and can fully meet the clinical requirements.

#### **Subject (Ethical requirements and informed consent)**

##### **Ethics Committee:**

Before the study begins, the study protocol and the informed consent of the subjects shall be submitted to the ethics Committee of the research unit for approval. The ethics committee shall hand over the approved informed consent to the investigator. Researchers should submit copies of the documents approved by the ERC and the membership and qualifications of the ERC to the sponsor. If there is any revision of the plan and informed consent, it also needs to be approved again by the ethics committee. Any serious adverse events that occur during the study should be reported by the investigator to the ethics committee. The ethics committee should be notified at the end of the study.

##### **Informed consent:**

Informed consent shall comply with the requirements of the latest version of the declaration of helsinki and the rules and guidelines formulated by the National Medical Products Administration of China. Subjects should be informed of the nature of the investigational drug, the purpose of the study, the possible benefits, and the possible risks before being screened. The investigator should explain the process and possible problems to the subjects clearly, and the subjects should sign and date the informed consent form to indicate their consent. Subject's verbal

consent, signed and dated by the witness, is obtained when a third party witness is permitted under special circumstances. The subject or his or her legal representative will retain one signed informed consent form and another signed informed consent form will be retained in the clinical investigator's study record.

**Inclusion criteria**

1. The voluntarily participate in the test and sign the informed consent approved by the ethics committee, and fully understand the purpose and requirements of the test.
2. Chinese adult males and females aged 18-50 (including 18 and 50), both male and female;
3. Body mass index (BMI) of 19.0-26.0 kg/m^2 (including the critical value); BMI= weight (kg)/height (m^2);

**Subject exclusion criteria:**

1. Subjects are allergic to the test drug or any component of the test drug or similar drugs, or have allergic constitution;
2. Vital signs examination, physical examination, clinical laboratory examination (blood routine test, urine routine test, blood biochemical test, serological test, etc.), 12-lead electrocardiogram, and the results are abnormal and clinically significant as judged by the researcher;
3. Subjects with a history of chronic or serious diseases such as liver, kidney, respiratory, blood or lymph, endocrine, immune (including HIV positive or other immune deficiency diseases), mental or gastrointestinal system, or surgery or disease that may affect drug absorption, distribution, metabolism or excretion;
4. Subjects have been assessed to be at risk of potentially difficult airway; Patients with past or current respiratory diseases such as bronchial asthma, chronic obstructive pulmonary disease, sleep apnea syndrome;
5. Subjects with past or current cardiovascular and cerebrovascular diseases such as postural hypotension, arrhythmia, hypertension and epilepsy;
6. Subjects with long QT syndrome or family history (grandparents, parents and siblings), or QTc interval > 450 ms; Indoor or left and right bundle branch block and/or QRS > 120ms; Ventricular ectopic beats were frequent ( $\geq$  1 premature ventricular beats occurred in ECG every 10s during screening period); Or abnormal resting heart rate (> 100 BPM);
7. Patients with history of anesthesia accidents;
8. Porphyria;
9. Patients who cannot tolerate venipuncture blood collection;
10. Scar constitution;
11. History of malnutrition or hypovolemic shock;
12. Subjects who have used any prescription drugs, non-prescription drugs, health care products, Chinese herbal medicine or Proprietary Chinese medicine within 2 weeks prior to screening;
13. Subjects used of sedatives, sleeping pills or other addictive drugs or positive results of drug abuse screening;
14. Subjects (including men) had fertility, sperm donation, egg donation plans or did not agree to use effective non-drug contraceptive methods during the study period and for 3 months after the study period;
15. Women of childbearing age whose blood pregnancy test results are higher than the normal range or those in lactation;
16. Participants who have consumed excessive amounts of tea, coffee and/or caffeinated beverages in the past for a long time (more than 8 cups per day, 1 cup =250mL), or cannot give up drinking tea, coffee and other beverages during the study period;

17. Smoked more than 5 cigarettes a day in the last 3 months or could not give up smoking throughout the study period;
  18. History of alcohol abuse in the 12 months prior to screening (i.e., more than 28 standard units per week for men and 21 standard units per week for women; 1 unit is equivalent to 285mL of beer, 25 mL of spirits, or 150 mL of wine), or those who drank regularly (more than 14 standard units per week) in the 6 months prior to screening, or who tested positive for alcohol breath, or who could not give up drinking throughout the study period;
  19. Subjects had donated blood or lost blood  $\geq 400$ mL within 3 months prior to screening, or who planned to donate blood during the study period and within 3 months after the study;
  20. Subjects had participated in clinical trials of other drugs within 3 months prior to screening, or plan to participate in clinical trials of other drugs during the study period;
  21. Subjects are expected to require surgery or hospitalization during the study period;
  22. The researcher considered that the subjects with abnormal pain sensation were not suitable for the study;
- Other circumstances that the investigator considers inappropriate for participation in this study.

## Research methods

### The main objectives of the study were as follows:

- 1.To investigate the safety and tolerability of long-acting ropivacaine injection in healthy subjects in a single subcutaneous injection of different doses;
- 2.To investigate the pharmacokinetics of long-acting ropivacaine injection during a single subcutaneous administration in healthy subjects;
- 3.The recommended single-point subcutaneous dose of long-acting ropivacaine injection was investigated.

### Secondary purpose:

- 1.To investigate the efficacy of single subcutaneous administration of long-acting ropivacaine injection in healthy subjects;
- 2.The analgesic onset time, duration and analgesic intensity of long-acting ropivacaine injection were investigated to determine the optimal dose spacing.

### Study design:

A randomized, single-blind, positive-controlled, single-dose subcutaneous, dose-increasing clinical study based on the characteristics of laparoscopic surgery.

**Test drug:** Long-acting ropivacaine injection Specification: 200mg/10mL; Manufacturer: Xi 'an Libang Pharmaceutical Co., LTD. Period of validity: 24 months;

**Control drug:** Ropivacaine hydrochloride injection, specification: 100mg/10mL; Manufacturer: AstraZeneca AB; Validity: 36 months.

**Number of planned subjects:** This study plans to enroll 50 healthy subjects, with unlimited male and female ratio. Whole blood and blank plasma samples were collected from 6 healthy subjects. An exploratory trial was conducted to investigate the optimal single point subcutaneous dose of long-acting ropivacaine injection in 3 healthy subjects. The safety, tolerability, pharmacokinetics, and pharmacodynamics of long-acting ropivacaine injection in a single subcutaneous administration of different doses were investigated in 41 healthy subjects.

### Dose design:

The guidelines for estimating the maximum recommended initial dose of drugs for the first clinical trial in healthy adult volunteers issued by the state food and drug administration (2012-05-15) and the relevant guidelines issued

by FDA were referred to. The initial dose was determined to be 150mg/ time. Referring to the pre-clinical pharmacodynamic test results of long-acting ropivacaine injection in SD rats, when the dose of ropivacaine was greater than or equal to 0.4mL (8mg), the pain threshold of rat heat stimulation was the highest at each time point after administration, and there was no significant difference. The estimated effective dose for human body was about 5.2 mg/kg, based on the adult body weight of 60kg. The clinical effective dose is about 300mg/ time. Maximum dose: 400 mg/ time.

### Methods for increasing dose:

**1. Exploration of optimal subcutaneous dose for single point of long-acting ropivacaine injection.** The initial single-point dose of the study included five doses: 0.6mL (12mg), 0.8mL (16mg), 1.0mL (20mg), 1.2mL (24mg) and 1.5mL (30mg), totaling 5.1mL (102mg). Three healthy subjects were given five different doses at different dosing sites in a single dose.

**2. Safety, tolerability and pharmacokinetics tests of single subcutaneous administration of long-acting ropivacaine injection at different doses:** based on preclinical animal test results, 150 mg was determined as the initial dose for healthy subjects. There are five cohorts from the lowest initial dose to the maximum dose, and the dose escalation scheme is shown in the table below.

**Table 1: Dose escalation protocol for single dose trials in healthy subjects**

| array | Dose (mg) | Number of healthy subjects (n)    |                                     |
|-------|-----------|-----------------------------------|-------------------------------------|
|       |           | Experimental group                | Control group                       |
|       |           | long-acting ropivacaine injection | ropivacaine hydrochloride injection |
| A     | 150       | 6                                 | 3                                   |
| B     | 230       | 8                                 | --                                  |
| C     | 300       | 8                                 | --                                  |
| D     | 350       | 8                                 | --                                  |
| E     | 400       | 8                                 | --                                  |
| Total |           | 38                                | 3                                   |

Positive control was set for cohort A, and no positive control was set for other dose groups. The study began at the minimum dose, with each subject receiving only one dose and only one dose cohort at a time. Safety assessments were conducted on days 7 and 21 after dosing, and the next cohort/batch trial was determined based on the results. If no significant adverse effects were observed in the maximum dose cohort (400mg), dose-escalation was not continued.

### Trial period:

This study was divided into three stages: screening period, trial period and follow-up period. The screening period was from -14 days before administration to -1 day before administration. Trial period: Trial 1 lasted from day 1 to day 2 of administration, and trial 2 lasted from day 1 to day 4 after administration. The follow-up period was after dosing (trial 1: Day 3; Experiment 2 was conducted from day 5 to day 21, with one follow-up on day 7 and day 21).

### Termination criteria:

1.If there is any SAE associated with the investigational drug during the course of the trial, the investigator and sponsor will fully discuss the cause and determine the impact on subsequent trials before deciding whether to continue the trial.

2. According to the Evaluation Criteria for Common Adverse Events (CTCAE) (V5.0, published on November 27, 2017), if  $\geq 1/2$  of the subjects in the trial cohort have grade  $\geq$  ii adverse events or  $\geq 1/3$  of the subjects have grade  $\geq$  iii adverse events (adverse events may be determined by the investigator to be related to the test drug), the investigator and the sponsor shall discuss. Whether to terminate dose escalation;
3. If no significant adverse effects were observed in the maximum dose cohort (400mg), dose escalation was discontinued.
4. The sponsor requested a complete termination of the test;
5. The National Medical Products Administration or the ethics committee ordered the trial to be terminated for some reason.

### Test Method:

#### **Optimal single point subcutaneous dose for long-acting ropivacaine injection:**

There were 3 healthy subjects. The six regions of the abdomen of each subject were marked as I, II, III, IV, V and VI clockwise from the xiphoid process.

The initial administration area was determined by computer randomization and marked clockwise as 1, 2, 3, 4 and 5. Five doses of the test drug were given subcutaneous single injection of 0.6mL (12mg), 0.8mL (16mg), 1.0mL (20mg), 1.2mL (24mg) and 1.5mL (30mg). Total 5.1mL (102mg); The sixth point is used as the blank comparison point. The local skin irritation reaction score and analgesic range of the administration site were investigated after subcutaneous injection of different doses of test drugs into the abdomen. At the same time observe the subjects areas of the adverse reactions and different doses of local skin irritation response, including clinical symptoms and signs, laboratory examination, adverse events (including systemic adverse reactions and the injection site appearance, pain or tenderness at the injection site, the injection site erythema or redness, injection site induration or swelling, itchy at the injection site, etc.).

The optimal single-point dose (L) and the average diameter (D) of the analgesic range of the dose were determined.

Only one dose was given at each injection site (from lowest dose to highest dose);

Only one dose was administered at each injection site;

Selection method of abdominal injection point: Through umbilical horizontal line, and on the left and right iliac spine to the belly line on the halfway point of the attachment for the two vertical line abdomen can be divided into six areas (figure 1), starting from xiphoid process parts respectively clockwise as I, II, III, IV, V, VI, freely choosing a point for each area injection points, the distance between any two points not less than 5 cm;

Local skin irritant reactions at the injection site: Local skin irritant reactions were observed at the injection site after administration, and implement the next administration or terminate the next dose after evaluation (the interval between two injections should be  $\geq 20$ min) :

- (1) When skin irritation is less than or equal to 2, the next dose can be injected;
- (2) When the skin irritation reaction was greater than or equal to 3 minutes, observe it once every 10 minutes until the skin irritation reaction was less than or equal to 2 minutes, record the time, and continue the next dose of injection;
- (3) Skin irritation reaction  $\geq 3$  points, and no relief was observed for 2 hours, the next dose of injection was terminated, and observation or follow-up was performed until the reaction disappeared; Evaluation of local skin irritation reaction at the injection site: During the test, local skin irritation reaction at the injection site was evaluated according to the skin irritation scoring system [30], which was scored 20min, 40min, 1h, 2h,

6h, and 24h after each administration. Local skin irritation reactions were determined and recorded according to the Evaluation Criteria for Common Adverse Events (CTCAE) (V5.0, published on November 27, 2017), including pain or tenderness at the injection site, erythema or redness at the injection site, induration or swelling at the injection site, and itching at the injection site. Subjects were hospitalized for observation for at least 12 hours after single dose.

[figure not shown]

Figure 1: Schematic diagram of six zones of abdomen

### **Safety, tolerability and pharmacokinetics of a single subcutaneous dose of long-acting Ropivacaine injection in healthy subjects:**

Each subject, on the basis of laparoscopic surgery in the abdominal area, according to the abdomen four partition method (i.e. through umbilical in vertical and horizontal stroke, the two lines intersect the abdomen is divided into four areas, as shown in figure 2) with four areas, from the xiphoid process position clockwise ordinal annotation for I, II, III, IV, random initial dosing area is determined, and in turn clockwise with dosing area for 1, 2, 3, The last area is the blank control area.

Any one point was chose in each area as the center of the circle (the distance between any two centers is not less than 80mm) and mark a circle with a diameter of 40mm.

The number of injection points in each queue was calculated by 1.2ml/needle. That is, the number of injection points in each queue = the dose of the queue /1.2, the number of injection points on each circle = the number of injection points in each queue /3, and the number of injection points on the first and second circles was determined by integer, and the remaining dose was allocated to the third circle.

Injection points on each circumference shall be evenly distributed; The labeled injection points were 1a, 1b, 1c. 2a,2b,2c ; 3a, 3b, 3c (the serial number of injection points on each circle should be ordered clockwise from the top of the circle, that is, from the head direction);

Mark the pain test area: mark the point on circle 1 or 2 where the center of the circle (1/2) is 1cm(A), 3cm(B) and 4cm(C) away from the center as the pain test point;

Each acupuncture measuring point was taken as the center of the circle, and a circle with a diameter of about 1cm was marked as the measurement area of acupuncture pain. The pain test areas were recorded as center 1 and center 2 respectively. 1aA,1bA,1cA ; 2aB,2bB,2cB ; 3aC,3bC,3cC ;

Acupuncture pain intensity was measured only on circle 1 and circle 2.

The test drug (test preparation or control preparation) shall be injected subcutaneously at a position enantiograms on the circumference; Observation of local skin irritation reaction at the injection site: The evaluation of local skin irritation reaction at the injection site was evaluated according to the skin irritation scoring system, and the scores were performed before and after administration at 20min,40min,1h,2h,6h,24h 48h 72h, as shown in the skin irritation reaction rating table.

Local skin irritation reactions, including pain or tenderness at the injection site, erythema or redness at the injection site, induration at the injection site, swelling at the injection site, itching at the injection site, etc., were determined and recorded according to the evaluation criteria for Common adverse events (CTCAE) (V5.0,

published on November 27,2017).

The onset time of analgesic maintenance time and the intensity of acupuncture pain were measured.

The linear distance between two adjacent injection sites on the same circumference was measured and recorded.

The drug administration investigator and the pain measurement investigator should not be the same person;

Subjects should be hospitalized for observation for 72 h after administration before discharge

[figure not shown]

Figure 2: Schematic diagram of four abdominal regions

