### **Pharmacodynamics index evaluation**

#### **Analgesic onset time:**

**Evaluation of analgesic onset time:** analgesic onset time was recorded as the time when the threshold of measured pain sensation was greater than the threshold of baseline pain sensation of the subject (i.e., baseline

VAS=4 average acupuncture pressure) when the pain sensation was measured after drug administration.

**Pain threshold:** the minimum stimulus intensity when the human body feels pain. Pain threshold usually refers to a stimulus intensity that can cause pain sensation in human body, which is generally divided into pain sensation threshold and pain tolerance threshold (the maximum stimulus intensity that human body can tolerate) .

**Duration of analgesia:** Effective analgesia refers to the pain threshold greater than the baseline pain threshold during pain measurement. Theoretically, the duration of analgesia is the difference between the effective start time and the effective end time of analgesia. However, in the actual operation of this study, real-time dynamic monitoring could not be achieved, so the duration of analgesia in this study was divided into minimum duration of analgesia and maximum duration of analgesia. The true value of analgesic duration was between the minimum duration and the maximum duration.

Minimum duration of analgesia = last time from measurement to effective analgesia - first time from measurement to effective analgesia

Maximum duration of analgesia = (last measured to effective analgesia +1) measurement time - first measured to effective analgesia time

**Table 3: Acupuncture pain intensity: The intensity of acupuncture pain in this study was divided into 3 levels as described in the table below:**

|              |                                                                                                                          |
|--------------|--------------------------------------------------------------------------------------------------------------------------|
| Three Grade  | Pain threshold was measured $\geq$ baseline VAS=6 acupuncture pressure                                                   |
| Second Grade | Baseline VAS=6 acupuncture pressure > threshold of pain sensation $\geq$ baseline VAS=5 acupuncture pressure             |
| First Grade  | Baseline VAS=5 acupuncture pressure value > threshold of pain sensation $\geq$ baseline VAS=4 acupuncture pressure value |

Analgesic range of injection site (Study 1);

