- 9) The coagulation function test included prothrombin time (PT), activated partial thrombin time (APTT), thrombin time (TT) and fibrinogen content (FIB). Check once during screening period.
- 10) Women must have a blood pregnancy test at screening and on day 4.
- 11) Routine urine examination should include glucose (GLU), ketone body (KET), protein (PRO), urinary occult blood (BLD), white blood cell (WBC), bilirubin (BIL), nitrite (NIT), pH, urochologen (UBG), specific gravity (SG); The screening period and the fourth day were examined once.
- 12) Pain test: measure the mechanical pressure value applied vertically when VAS=4.
- 13) Alcohol breath test and drug abuse screening (including morphine, methamphetamine, ketamine, methylene dioxy-amphetamine, THC) should be performed once a day.
- 14) 12-lead electrocardiogram was examined once during screening period, once on day -1 and once on day 4.
- 15) When necessary.
- 16) Collect drug combination data, including drug dose, route of administration, administration schedule, start date, indication, and end date, and record the data from the beginning of the trial until the end of follow-up.
- 17) After screening, subjects should be asked whether they suffer from acute diseases; Have you taken any alcohol-based products in the 24 hours prior to study administration; Whether you exercise vigorously; Whether to maintain a good living condition; Drink (or consume) theophylline, caffeine, theobromine, and alcohols 48 hours before administration of the study drug.
- 18) Collection of blood pharmacokinetic samples: Blood pharmacokinetic samples were collected at 0.5h, 1h, 1.5h, 2h( $\pm 2$ min), 4h, 6h, 8h, 10h, 12h, 21h, 24h, 27h, 30h, 33h, 36h, 48h and 72h( $\pm 5$ min) after 15min before administration.

- 19) Acupuncture pain intensity was measured before and after administration at 15min, 1h, 4h, 8h, 10h, 12h, 14h, 21h, 24h, 27h, 30h, 33h, 36h, 48h and 72h (the time window of measurement point from 15min to 72h was  $\pm 15$ min).
- 20) Local skin irritation at the injection site: scores were scored before and after administration 20min, 40min, 1h, 2h, 6h, 24h, 48h and 72h (the time window from 20min to 1h observation point was  $\pm 3$ min; The observation time window from 2h to 72h is  $\pm 5$ min).
- 21) When subjects withdraw from the study, they should be checked as far as possible according to the safety evaluation on the fourth day after the end of drug administration to complete the withdrawal visit.

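### The Test 2 pain-area codes contradict the sentences around them: followed as printed, the 4 cm areas are never tested and 1 cm against 3 cm cannot be separated from circle

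*Protocol*

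**What the plan says.** The layout is set out in the Protocol under Test Method, in the section on safety, tolerability and pharmacokinetics of a single subcutaneous dose (Test 2).

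- **Marking rule:** "mark the point on circle 1 or 2 where the center of the circle (1/2) is 1cm(A), 3cm(B) and 4cm(C) away from the center".
- **Code list for the marked areas:** "1aA,1bA,1cA ; 2aB,2bB,2cB ; 3aC,3bC,3cC". The digit is the circle and the small letter is the injection point; for the letters, "the serial number of injection points on each circle should be ordered clockwise from the top of the circle".
- **Where pain is tested:** "Acupuncture pain intensity was measured only on circle 1 and circle 2".
- **How many injection points there are:** "The number of injection points in each queue was calculated by 1.2ml/needle". The total is divided by three, with the split made as follows: "the number of injection points on the first and second circles was determined by integer, and the remaining dose was allocated to the third circle".

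Under Pharmacodynamics index evaluation, "analgesic onset time was recorded as the time when the threshold of measured pain sensation was greater than the threshold of baseline pain sensation". Duration runs from the first to the last effective measurement, with a minimum and a maximum version. Neither definition says how several areas in one subject become one time. Under Pharmacodynamics analysis, the mixed model lists group, administration or blank area, visit and the group-by-visit interaction; distance is not listed.

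**The concern.** The code list disagrees with the sentence before it and the sentence after it. This is operative text: it decides where the skin is marked and which points are pricked. An SAP can choose how to analyse the readings, but it cannot recover readings at a distance that was never tested, or undo a confounding built into the marking.

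The Secondary purpose section wants onset, duration and intensity in order to determine dose spacing. How far analgesia reaches from the injection ring bears directly on that. If distance is lost or tied to a single circle, the study is weakened on that aim.

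The most natural way to repair the codes, marking all three distances at every injection point on circles 1 and 2, brings a second difficulty. The number of injection points rises with injected volume, so cohorts and arms would be tested on different numbers of areas.

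**Working it through.** **1. Codes against the two sentences.** Nine codes are listed. Three (3aC, 3bC, 3cC) are on circle 3, which is not tested, and they are the only C codes. Six remain: 1aA, 1bA, 1cA at 1 cm and 2aB, 2bB, 2cB at 3 cm. Every 1 cm reading is then on circle 1 and every 3 cm reading on circle 2. Distance and circle are the same variable, and 4 cm has no reading.

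**2. Concentration check.** Test drug is 200 mg/10 mL = 20 mg/mL. The protocol's own Test 1 total reproduces: 0.6 + 0.8 + 1.0 + 1.2 + 1.5 = 5.1 mL, and 5.1 × 20 = 102 mg, as stated. Control is 100 mg/10 mL = 10 mg/mL.

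**3. Area counts if A, B and C are marked at every injection point on circles 1 and 2.** Volume = dose / concentration; points = volume / 1.2; points per circle = points / 3, taken as an integer; areas = 2 circles × points per circle × 3 distances. The protocol does not say whether the integer is truncated or rounded, so both are shown where they differ.

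| Group | Volume (mL) | Points | Per circle | Integer | Areas tested |
|---|---|---|---|---|---|
| 150 mg test | 7.5 | 6.25 | 2.08 | 2 | 12 |
| 150 mg control* | 15.0 | 12.5 | 4.17 | 4 | 24 |
| 230 mg | 11.5 | 9.58 | 3.19 | 3 | 18 |
| 300 mg | 15.0 | 12.5 | 4.17 | 4 | 24 |
| 350 mg | 17.5 | 14.58 | 4.86 | 4 or 5 | 24 or 30 |
| 400 mg | 20.0 | 16.67 | 5.56 | 5 or 6 | 30 or 36 |

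*Assumes 150 mg of control given at the same 1.2 mL per needle.

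From 150 to 400 mg the count rises 2.5 to 3 times. In cohort A, the only randomised comparison, control has twice the areas of test drug. At 150 mg of test drug there are only two points per circle, so the listed 1c and 2c do not exist.

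**4. Would the count matter?** That depends on the rule for combining areas. As an illustration, onset and duration were simulated on the Test 2 reading times given under Observation indicators. The true effect was the same in every area, and a subject counted as analgesic if any area was. Assumed inputs, none from the protocol: mean onset 2 h, mean end of effect 18 h, coefficient of variation 40%.

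| Between-area correlation | Mean minimum duration, 12 areas (h) | 24 areas (h) | 36 areas (h) | Onset earlier, 12 to 36 areas (h) |
|---|---|---|---|---|
| 0 | 27.1 | 31.4 | 33.6 | about 1.1 |
| 0.5 | 21.6 | 24.3 | 25.7 | about 0.5 |
| 0.8 | 17.7 | 19.0 | 19.8 | about 0.2 |
| 1.0 | 12.0 | 11.9 | 11.9 | 0 |

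The average over areas did not change with their number (about 18 h for end of effect throughout).

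**The case against.** The strongest reply is that the code list is a translation slip or a shortened example. The sentences before and after it agree on circles 1 and 2, the test areas are also recorded as belonging to centres 1 and 2, and the list stops at letter c although the needle rule gives 4 to 6 points per circle at higher doses. The figure showing the abdominal regions is not reproduced and might settle the layout. This is fair and makes the literal reading less likely to be the intended one. It does not remove the contradiction: staff mark subjects from this text, and different readings between batches or cohorts would yield data that cannot be compared.

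It can also be said that combining areas is a matter for the SAP and that these are secondary measures in a 41-subject phase I test with 3 controls. Both points stand and limit the weight of the concern. Neither reaches the question of which areas are marked and tested.

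A reader might infer three stronger things that the document does not support.

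- **That onset, duration and distance effects are distorted whichever way the text is read.** By code, distance is lost or confounded, but no dose-related bias in onset or duration is shown. On the other reading, the three distances stay balanced within each subject, and onset and duration are affected only under an any-area rule that the protocol does not state.
- **That each extra area adds a chance of false analgesia from one mistaken answer of weaker.** Under Acupuncture pain intensity measurement, that answer leads to the next pressure. If that one feels stronger, the previous pressure, the VAS=4 baseline, is recorded. This is not above baseline, so it is not effective analgesia. Areas in one subject are also unlikely to be independent.
- **That the larger sets cannot be completed in time.** Table 10, note 19 says "the time window of measurement point from 15min to 72h was" ±15 min, but no time per area is given anywhere.

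**Conclusion.** The point holds in a limited form. The area codes are wrong as written, because they cannot be reconciled with the marking rule and the testing rule beside them. Followed as printed, they lose all 4 cm readings and make 1 cm against 3 cm a comparison of circle 1 with circle 2. That conclusion needs no assumption beyond the protocol's own labelling.

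The second part is conditional. If every distance is marked at every injection point, area counts differ by volume as tabulated; the control figure rests on 1.2 mL per needle in both arms. Whether onset and duration would then move with area count depends on a combining rule that the protocol leaves open. The size would depend on between-area correlation: in the illustration, from 12 to 36 areas, mean minimum duration lengthens by about 4 h at correlation 0.5 (25.7 − 21.6), about 2 h at 0.8 (19.8 − 17.7), and not at all at 1. These figures show direction and are not estimates for this trial.

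**What to change.** 1. Correct the code list so that A, B and C are each marked and tested on both circle 1 and circle 2, and delete the circle 3 codes.
2. Use the same number of areas per circle and distance in every cohort and in both arms. One way is to use injection point a only: 1aA, 1aB, 1aC, 2aA, 2aB, 2aC, six areas per subject.
3. Derive onset and duration by a rule that does not depend on the number of areas, for example at one named distance. If the two circles are combined, the rule must cover a circle that never reaches onset or is still analgesic at 72 h; a simple average does not.
4. State whether the distance of interest is from the circle centre or from the needle. With a 2 cm radius, on the line through an injection point, A and B are both 1 cm from the needle (2 − 1 and 3 − 2) and C is 2 cm from it (4 − 2). A and B then differ in lying inside or outside the ring, not in distance from the drug.

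The cost is protocol wording and a marking template. Readings per time point fall, and the price is fewer replicate areas per subject at the higher doses.
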